**Grant Type:**

First Submitted Proposal Grant

**Field:**

Other

**Priority:**

Other

**Is this an animal study?**

No

**Keywords:**

functional voiding dysfunction, interferential electrical stimulation, interferential stimulation, urodynamic, uroflowmetry, women

**Persian Title:**

بررسی تاثیر جریان اینترفرنشیاال بر علائم بالینی و یافته های یورودینامیک در زنان مبتلا به اختلال تخلیه ادرار: یک کارآزمایی بالینی

**Is this project a clinical trial?**

Yes

**University social responsibility**

No

**English Title**

Investigating the effects of interferential stimulation on clinical symptom and urodynamic findings in women with voiding dysfunction: A randomized clinical trial

### **Selected Keywords**

#### **Research Line**

Pelvic Floor Physiotherapy

#### **Keywords**

Voiding Dysfunction, Functional voiding Dysfunction, Interferential Electrical Current, Interferential stimulation, Urodynamics, Uroflowmetry, Women

---

### **Type of project**

Practical research

### **Introduction-Problem Statement**

#### **Introduction**

Incomplete bladder emptying is a prevalent clinical issue in women, associated with impaired bladder voiding (1). Due to variations in methodology and definitions across studies, there is no precise estimation of its prevalence. However, urodynamic findings suggest that up to 2% of adults are affected by this condition (2). The prevalence of voiding dysfunction in women ranges from 6.8% to 61.7%, depending on diagnostic criteria, and increases with age (3). This disorder encompasses symptoms experienced during or after voiding, with the most frequently reported being a sensation of incomplete emptying, followed by weak urinary stream. In some cases, it may coexist with storage-phase symptoms. In these cases the underlying pathology may be either independent or interrelated (1, 2, 4).

Normal micturition begins with a voluntary reduction in intraurethral pressure due to relaxation of the urethra and surrounding striated muscles. This is followed by sustained contraction of the detrusor muscle, leading to complete bladder emptying within a defined period. Thus, normal voiding is characterized by an unobstructed, rapid flow with minimal post-void residual (PVR) volume, achieved through urethral relaxation without elevated detrusor pressure (2).

The primary causes of voiding dysfunction are either impaired detrusor contractility or bladder outlet obstruction (BOO) (1). A prospective study found that most cases

are attributed to BOO (2). BOO is defined as increased detrusor pressure and decreased urinary flow rate during voiding, in the absence of infection or obvious injury. It may be associated with elevated PVR (2, 5). In women, BOO arises from structural or functional etiologies. The main functional causes are dysfunctional voiding (DV) and detrusor-sphincter dyssynergia (DSD) (1).

According to the International Continence Society, DV is characterized by intermittent or fluctuating urinary flow due to involuntary contractions of the periurethral striated muscles during voiding in neurologically intact individuals. DSD, as a neurological disorder, involves involuntary coincidence of urethral or periurethral striated muscle contractions with detrusor contraction. This sometimes leading to complete urinary interruption (5, 6). DSD is observed in patients with spinal cord injuries affecting the brainstem and sacral spinal cord relations (7).

### **Problem Statement**

BOO is typically diagnosed via pressure-flow studies assessing urinary flow rate and detrusor pressure (2). In women, a bladder outlet obstruction index (BOOI) >18 indicates obstructive voiding dysfunction. Elevated PVR (>50 mL) and excessive daytime urinary frequency are key evaluable symptoms (8, 9). Patients often face challenges such as frequent bathroom visits, sleep disruption, and persistent daytime anxiety (10). Chronic or acute urinary retention (painful or painless) and urinary tract infections are additional complications (1).

Definitive diagnosis of voiding dysfunction relies on patient history and urodynamic testing (1). A 3-day voiding diary, uroflowmetry, ultrasound-determined PVR, pelvic floor electromyography (EMG) to differentiate structural from functional obstruction, and endoscopic evaluation are clinical diagnostic tools for voiding dysfunction (1, 11). PVR and bladder emptying efficiency are commonly used to assess treatment efficacy in voiding dysfunction, including BOO (12). Studies indicate that symptoms alone are unreliable for diagnosis of this dysfunction. Abnormal uroflowmetry and pressure-flow studies are essential to distinguish between impaired detrusor contractility and BOO. A maximum flow rate <15 mL/s and PVR >50 mL are reliable diagnostic markers for voiding dysfunction (9).

In voiding dysfunction, treatment aims to normalize voiding patterns and prevent complications. First-line therapies for functional voiding dysfunction include pelvic floor physiotherapy and biofeedback. Additional options (though lacking robust evidence) include psychological interventions, medications such as alpha-blockers, botulinum toxin injections, and GABA agonists (2). Intermittent catheterization (CIC) and electrical stimulation (invasive or noninvasive) are also employed (1).

Neuromodulatory electrical currents target lower urinary tract dysfunction by modulating neural control. Methods include pelvic floor electrical stimulation (vaginal, anal, or surface electrodes), interferential current (IFC), magnetic stimulation, percutaneous tibial nerve stimulation (PTNS), and sacral nerve stimulation (SNS) (13). These modalities enhance bladder capacity, relax pelvic muscles, and reduce bladder pressure (14). In voiding dysfunction, they increase bladder capacity due to the inhibition of pelvic reflexes. Electrical currents decrease sympathetic overactivity via pudendal nerve stimulation. So, they can reduce involuntary pelvic floor contractions. Because of essential role of pelvic floor muscles on sacral reflexes, stimulation of this region with IFC can impact on bladder function (15).

IFC employs two medium-frequency (1–10 kHz) out-of-phase sinusoidal currents. Their high frequency reduces skin impedance, generating a low-frequency interference current in deeper tissues (16). Session duration varies but typically lasts 20–30 minutes for non-acute conditions (17).

Despite clinical studies on IFC for pelvic disorders (e.g., urinary incontinence, constipation) (13, 18, 19), no research has examined its effects on female voiding dysfunction, though recent pediatric studies exist (14, 20). So, this study investigates IFC's effects on lower urinary tract symptoms (LUTS) and uroflowmetry in women with voiding dysfunction. Participants will be randomized into treatment and sham groups. Both will receive standard care (medication, urotherapy, and functional voiding exercises). Urotherapy includes education on urinary tract function, fluid intake, scheduled voiding (every 2–3 hours), and proper toileting. The treatment group will receive 10 sessions of real IFC, while the control group will undergo sham IFC. Post-treatment clinical assessment and clinical evaluations consist of uroflowmetry and PVR will use to investigate the treatment efficacy. If IFC proves effective for functional voiding dysfunction, it may emerge as a noninvasive therapeutic option.

### **Summary of the necessity of implementing the project**

Regarding the use of interferential electric current as a current that modulates neural pathways in various pelvic floor disorders, including urinary incontinence, theoretical foundations support the use of this current based on increasing the activity of urethral sphincter afferents and causing relaxation in pelvic floor muscles in urinary incontinence (1, 2). Despite the existence of limited studies on the use of interferential current in urinary incontinence in the pediatric population, no study in this area was found in the female population with this disorder (1, 3). Given the impact on quality of life and the possibility of developing infection and chronic pain if

left untreated (4), the need to investigate the effect of interferential current in women with functional urinary retention as a non-invasive treatment option is clearly evident.

## **Summary of Methodology and Analysis**

### **Study Design**

Following ethical approval, a non-probability convenience sampling method will be employed. A urologist will evaluate patients with voiding dysfunction through:

- **Clinical history** (symptom assessment)
- **Neurological examination** (anal tone, voluntary anal control, genital/limb reflexes, sensory evaluation)
- **Urodynamic tests** (cystometry for detrusor pressure, uroflowmetry and pre-/post-void ultrasound to classify voiding dysfunction)

Eligible patients will complete a 3-day voiding diary (recording fluid intake, voiding frequency, and urinary patterns). They will then be referred to the physiotherapy clinic of rehabilitation faculty of Iran university of medical science with all of medical records. The urologist will remain blinded to group allocation. At the physiotherapy clinic, all participants will first receive a comprehensive explanation of the entire procedure and the purpose of the study. Then, individual informed consent forms will be obtained from each participant. Patients will be informed that there are two treatment groups, and except for the method of applying the interferential electrical current, all treatments in both groups are similar. Group assignment will be completely random, with an equal chance of being placed in either group. They will also be assured that if significant improvements are observed at the end of the study, the treatment received by the other group will be fully provided to them.

A completed 3-day urinary diary will be collected from each patient, and from this data, the frequency of bathroom visits within 24 hours will be extracted. Using a computerized random number list, patients will then be randomly assigned to either the treatment or control group in a 1:1 ratio, using blocks of four.

Next, a self-developed questionnaire collecting personal information such as age, height, and weight will be completed by all patients in both groups at the beginning of the first session. Afterward, all patients will receive the Persian versions of the female lower urinary tract symptom (FLUTS-ICIQ) and pelvic floor distress inventory-20 (PFDI-20) questionnaires to score the severity of their lower urinary tract symptoms and pelvic floor symptoms, respectively.

At the final treatment session, the Persian version of FLUTS-ICIQ and PFDI-20 questionnaires will be administered again to compare patients' scores on symptoms before and after treatment. Additionally, patients will complete the Persian version of the Patient Global Impression of Change (PGI-C) questionnaire to self-assess overall changes in their condition after treatment.

Finally, patients will be asked to complete the 3-day urinary diary once more. Two weeks after completing treatment, they will return for a visit with the urology specialist to undergo uroflowmetry testing, clinical examination, and evaluation of symptoms.

Moreover, a 3-month follow-up period is included in this study. After this period, uroflowmetry testing will be repeated once more, and clinical symptoms will be reassessed to evaluate the long-term effects of routine urotherapy alone versus routine urotherapy combined with IFC on clinical symptoms and uroflowmetry findings in patients with functional voiding dysfunction

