### **Statistical Analysis**

Descriptive information regarding the demographic characteristics of individuals in both groups will be given as means (standard deviations) for quantitative variables and as frequencies (percentages) for qualitative variables. For comparing of each demographic variable between the two study groups, the independent t-test for normally distributed quantitative variables and the Mann-Whitney test for non-normally distributed quantitative variables will be applied. The chi-square test will be conducted to compare qualitative variables.

The normality of the data in the study groups will be tested using the Shapiro-Wilk test. To comprehensively examine the extracted data, the following procedures will be carried out, as elaborated below.

To compare the mean of each variable in both groups before the intervention, two weeks after the intervention, and after a three-month follow-up period, the two-way repeated measures ANOVA will be employed, assuming the data are normally distributed. In the case of non-normality, a nonparametric equivalent will be used.

For the comparison of the mean of the variables between both groups at every time point (before the intervention, at two weeks after the intervention, and after a three-month follow-up), the two independent sample t-test will be used if the data is normally distributed and the Mann-Whitney test if the data is distributed non-normally.

To determine differences in the mean of the variables of both groups over the study period, the one-way repeated measures ANOVA will be used. In the presence of a statistically significant difference in the variable mean over time, the post hoc test with Bonferroni and Tukey corrections will be utilized. The data will be analyzed using SPSS version 26 software. The significance level in this study is assumed to be 5%.

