#### 5. Interferential Current (IFC)

- **Conceptual Definition:**  
A low-frequency (1–100 Hz), amplitude-modulated current generated by interference of two medium-frequency (1–10 kHz) currents. It penetrates deep tissues by overcoming skin impedance (16, 18). It is Recommended to use this current for 20–30 minutes per session for non-acute conditions (19).
- **Operational Definition:**
  - Device: Standard electrotherapy unit (Novin, Iran).
  - Parameters:
    - Carrier frequency: 4,000 Hz
    - Beat frequency: 80–160 Hz
    - Duration: 20 minutes (pelvic region).

- Electrode placement: Cross-shaped over pubic symphysis and ischial tuberosities.
- Intervention protocol:
  - Real IFC group: Current intensity adjusted as high as possible according to patient tolerance.
  - Sham IFC group: Current applied for 1 minute in the first sensation of patient, then discontinued (27).

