### 3. Interventions

#### All Participants Receive:

- **Standard Urotherapy (10 sessions, 20 mins/session, 2x/week):**
  - Education on urinary tract function
  - Fluid management (1.5–2 L/day)
  - Scheduled voiding (every 2–3 hours)
  - Proper toileting posture (spinal alignment, foot support)
  - Pelvic floor muscle training (10-sec contraction + 30-sec relaxation).

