### Assessment Timeline:

- **Baseline:** Pre-treatment.
- **Post-Treatment:** After 10 sessions (5 weeks).
- **Follow-Up:** 3 months post-treatment.

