### **Protocol Deviations Management**

- **Non-Adherence:** Participants missing >2 sessions excluded from per-protocol analysis.
- **Adverse Events:** Documented and reported to ethics board (e.g., skin irritation from electrodes).

This protocol aligns with CONSORT guidelines for non-pharmacological trials. Let me know if you need additional operational details!

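### Post-baseline assessments are triggered by completing treatment, with no calendar anchor or window, so women who stop early have no clear assessment date and women who fall behind may be measured later

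*Protocol*

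**What the plan says.** The protocol's Study Design section sets two triggers after baseline.

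- For symptom scores: "At the final treatment session, the Persian version of FLUTS-ICIQ and PFDI-20 questionnaires will be administered again". The PGI-C is given at the same point and the diary is repeated after it.
- For uroflowmetry and examination: "Two weeks after completing treatment, they will return for a visit with the urology specialist to undergo uroflowmetry testing".

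The Assessment Timeline gives the post-treatment point as "After 10 sessions (5 weeks" and the follow-up as "3 months post-treatment". The Statistical Analysis section compares the groups "before the intervention, at two weeks after the intervention, and after a three-month follow-up".

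The planned schedule is "10 sessions, 20 mins/session, 2x/week". The only rule for non-adherence, under Protocol Deviations Management, is: "Participants missing >2 sessions excluded from per-protocol analysis". That rule concerns an analysis set. It does not say when, or whether, those women are assessed. No section gives a visit window, a date counted from randomisation, or an assessment date for a woman who stops or is delayed.

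**The concern.** When the outcome visit depends on something that happens after randomisation, the women who reach it, and the time at which they reach it, can depend on the arm. Here the triggers are the final session and the completion of treatment. A woman who stops halfway does not clearly meet either, and all the listed primary endpoints (Qmax, voiding time, PVR and ICIQ-FLUTS) hang on them.

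The arms differ in what a woman experiences at each session. For real stimulation the protocol says: "Current intensity adjusted as high as possible according to patient tolerance". Sham is one minute at first sensation and then off. Loss or delay that differs by arm is therefore possible. If it occurred, the comparison would be between selected groups, or between women measured at different times since randomisation. In addition, a repeated-measures ANOVA in its standard form uses only women with all time points, so one undefined visit can remove a woman from that comparison altogether.

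**Working it through.** **Timing.** The inputs are 10 sessions at 2 per week (All Participants Receive), uroflowmetry two weeks after treatment (Study Design) and follow-up at 3 months after treatment (Assessment Timeline). I assume that the first session coincides with randomisation and take 3 months as 13 weeks.

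- Treatment lasts 10 / 2 = 5 weeks, which reproduces the protocol's own figure.
- Uroflowmetry falls at 5 + 2 = week 7.
- Follow-up falls at 5 + 13 = week 18.

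The protocol does not mention making up missed sessions. If m sessions were missed and made up at the same rate, session 10 would fall at week (10 + m) / 2 and uroflowmetry two weeks later:

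| Missed and made up | Session 10 | Uroflowmetry |
|---|---|---|
| 0 | week 5 | week 7 |
| 2 | week 6 | week 8 |
| 4 | week 7 | week 9 |

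Each made-up session costs 7 / 2 = 3.5 days, so a few missed sessions shift the visit by one to two weeks.

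**Number without a clear date.** The planned total is 2 × 14 = 28. The protocol gives no rate of stopping. If 10–20% stopped early (assumption), that is 2.8 to 5.6, or about 3 to 6 women. Each is 1/14, about 7%, of an arm.

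**Precision.** The 14 per group under Sample Size Calculation Method cannot be reproduced, because no endpoint, difference, standard deviation or sidedness is stated. Working backwards at two-sided 5% and 80% power, 14 per group implies a standardised difference d = √(2/14) × (1.960 + 0.842) = 1.06. Power is then Φ(d / √(1/n₁ + 1/n₂) − 1.960):

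| Lost (assumed) | From each arm | From one arm only |
|---|---|---|
| 0 | 0.80 | 0.80 |
| 2 | 0.74 | 0.77 |
| 3 | 0.70 | 0.75 |
| 4 | 0.66 | 0.725 |

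**Bias.** If a fraction f of one arm is lost and those women differ from completers by g standard deviations, the completer mean is off by f × g. I take g from 0.25 to 1.0 (assumption).

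- 2 of 14 lost: 0.143 × 0.25 = 0.04 SD, up to 0.143 × 1.0 = 0.14 SD.
- 4 of 14 lost: 0.286 × 0.25 = 0.07 SD, up to 0.286 × 1.0 = 0.29 SD.

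**Post-treatment point.** The Assessment Timeline places it after the tenth session, nominally week 5. The Statistical Analysis section places it two weeks later, nominally week 7. Study Design splits it, with questionnaires at the final session and uroflowmetry at two weeks. For ICIQ-FLUTS, a primary endpoint, the time of collection and the analysed time point therefore do not match.

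**The case against.** Measuring at a fixed interval after the last session is a coherent choice for a short treatment with the same planned schedule in both arms, and the timeline's 5 weeks gives an approximate calendar time. That is fair, and with full attendance nothing goes wrong.

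Three stronger readings are tempting, and the documents do not support them.

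- A reader might infer that loss depends on tolerance of the current. No passage says so. Intensity is set within each woman's tolerance, and the Group-Specific Protocols table describes a level that remains comfortable, which works against stopping for that reason. The only attrition the protocol foresees is put down to the follow-up period.
- A reader might infer that women who stop are never measured. The protocol is silent. A woman's last attended session could be read as her final session, and excluding women from a per-protocol analysis suggests that they have data.
- A reader might infer that assessment after ten sessions contradicts a rule that tolerates two missed sessions. One is a time point and the other a threshold for an analysis set. A woman with eight of ten sessions can still be assessed at the end of the five weeks.

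It is also fair that late and missing visits need different assumptions: if sessions are not made up, the visit does not slide. Supervised urotherapy is fixed at ten sessions, so delay adds elapsed time and home practice but no further supervised sessions. The definition of the main analysis set may stand in an analysis plan that is not shown.

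The visit schedule itself remains open to criticism. It is protocol content, and as written it gives no clear date to a woman who does not complete treatment.

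**Conclusion.** The concern holds as a weakness in the visit schedule that should be corrected. All post-baseline assessments hang on treatment completion, without a calendar anchor or window. Early stopping leaves the date of the primary endpoints unclear, and falling behind may delay them. Differential loss or delay between arms is a risk that follows from the design and is not a demonstrated effect.

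Undefined visits after early stopping are the larger exposure. On assumed losses of 2 to 4 per arm, power falls from a nominal 80% to 74–66%. On assumed losses of 2 to 4 from one arm, bias runs from 0.04 to 0.29 SD. Drift from 2 to 4 made-up sessions is one to two weeks. These figures rest on assumed losses, an assumed gap between lost women and completers, the standardised difference implied by 14 per group, and an assumption that sessions are made up.

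**What to change.** Schedule the post-treatment and 3-month assessments by weeks from randomisation, nominally week 7 and about week 18, each with a window such as ±1 week. Apply this to every randomised woman whatever number of sessions she received, subject to her right to withdraw. State that she is analysed in her randomised group, and that the rule on more than two missed sessions defines only a supportive per-protocol analysis.

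Reconcile Study Design, Statistical Analysis and the Assessment Timeline on the post-treatment point. In particular, say whether ICIQ-FLUTS, PFDI-20 and PGI-C are taken at the end of the 5-week treatment period or at the two-weeks-after visit that the analysis uses.

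The cost is protocol wording and scheduling. Women who complete treatment need no extra tests, and those who stop are invited to the same visits as everyone else. The downside is that a woman who falls behind may be measured less than two weeks after her last session. A window to week 8 keeps the full two weeks for up to two made-up sessions (session 10 at week 6). With four made up, session 10 falls at week 7, and at most one week remains.
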